## Outcomes measurement

Blood tests, BP, anthropometric measurements, and a health assessment questionnaire, will be conducted both at baseline and 6 months after randomization. Additionally, participants will receive a shorter follow-up questionnaire at 3 months.

### Primary outcome

#### LS7 score

The primary outcome is the LS7 score at 6 months compared with baseline, analyzed as the mean ± SD and mean difference. The LS7 scores consists of seven health metrics including physical activity, diet, smoking, BMI, TC, BP, and FBG [32]. Each LS7 score metric is evaluated as poor (0 point), intermediate (1 point), or ideal (2 points). The scoring scheme is as follows: physical activity (ideal: ≥ 150 min/week moderate or intense level of exercise, intermediate: 1–149 min/week moderate to vigorous level of exercise, poor: none—sedentary); diet (ideal: 4–5 components, intermediate: 2–3 components, poor: 0–1 components; the diet components refer to the following: at least 4.5 cups per day of fruits/vegetables, or at least 3.5-oz servings of fish per week, or less than 1500 mg/day of sodium consumption per day, or less than 450 kcal (36 oz) per week of sweets/sugar-sweetened beverages, or less than 3 servings per day of whole grains); smoking (ideal: never smoked or quit more than 12 months ago, intermediate: former smoker, but quit within 12 months, poor: current smokers); BMI (ideal: ≤ 22.9 kg/m^2^, intermediate: 23–24.9 kg/m^2^, poor: ≥ 25 kg/m^2^); TC (ideal: < 6.2 mmol/L, intermediate: 6.2–7.9 mmol/L, poor: > 7.9 mmol/L); BP (ideal: SBP < 120 mmHg and DBP < 80 mmHg, intermediate: SBP: 120–134 mmHg or DBP: 80–84 mmHg, poor: SBP ≥ 135 mmHg or DBP ≥ 85 mmHg); and FBG (ideal: < 5.6 mmol/L, intermediate: 5.7–6.9 mmol/L, poor: ≥ 7.0 mmol/L). These individual scores are then added together to form a composite score that ranges from 0 to 14 [41–44]. The LS7 score was validated against the Pooled Cohort Equation (PCE), which was considered as the golden standard tool on predicting 10-year CVD risk, on prediction to CVD and all-cause mortality [45]. A higher LS7 score signifies better cardiovascular health [46]. LS7 score will be further categorized into poor (0–4), intermediate (5–9), and ideal [10–14, 41].

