### Inclusion and exclusion criteria

The inclusion criteria are as follows: (1) aged between 35 and 59 and (2) at risk of NCD development defined by at least two components of the following: 1. Body mass index (BMI) ≥ 23 kg/m^2^, 2. Diet (less than 4 components of healthy diet defined by LS7, please refer to “Primary outcome” for the detail), 3. Physical activity (< 150 min of moderate or intense level of exercise per week), 4. Smoking status (current smokers or former smokers quit within 12 months), 5. Family history of HT/DM/CVD in 1 st degree relative < 60 years of age, 6. Alcohol Use Disorders Identification Test-C (AUDIT-C) score ≥ 5, and 7. Total cholesterol (TC) level (6.2 mmol/L ≤ TC < 8 mmol/L).

The exclusion criteria are as follows: (1) unable to provide consent; (2) pregnancy; (3) do not understand Cantonese; (4) measured with blood lipid level (TC ≥ 8 mmol/L; LDL ≥ 5 mmol/L; triglyceride (TG) ≥ 5 mmol/L); (5) blood pressure (BP) (SBP ≥ 135 mmHg or diastolic BP (DBP) ≥ 85 mmHg); (6) QRISK-3 ≥ 15%; (7) with doctor-diagnosed chronic diseases and require medication (including DM, HT, CVD), chronic obstructive pulmonary diseases (COPD), depression, autoimmune diseases, and cancer.

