**B component**			
BP^a,c^	SBP 120–129 mmHg or DBP < 80 mmHg	SBP 130–134 mmHg or DBP 80–84 mmHg	SBP ≥ 135 or DBP ≥ 85 mmHg
FBG^a^	< 5.6 mmol/L	5.6–6.9 mmol/L	≥ 7 mmol/L
Blood lipids	–	–	TC ≥ 8 mmol/l or TG ≥ 5 mmol/l or LDL ≥ 5 mmol/l
CVD risk	–	–	QRISK3-2018 ≥ 15%
Definition	Not meeting “high-risk” criteria	At least 2 A components and 1 B component above	At least 1 B component above

^a^AHA simple 7 criteria risk factors [91]

^b^The five diet components are as follows: (1) 4.5 cups per day of fruits/vegetables, (2) servings of fish per week (3.5-oz servings), (3) 1500 mg/day of sodium, (4) 450 kcal (36 oz) per week of sweets/sugar-sweetened beverages, and (5) 3 servings per day of whole grains (1.1 g of fiber in 10 g of carbohydrate; 1-oz equivalent servings) [91]

^c^AOBP measurement [47]: Take mean BP readings with 1 min interval between readings. Use the average of this 3 readings. Measurement conditions: 1) Quiet room with comfortable temperature; 2) No smoking, caffeine, food, or exercise for 30 min before measurement; 3) Remain seated and relaxed for 3-5 min; 4) No talking by patient or staff during or between measurements. Measurement posture: 1) Sitting with back supported by chair; 2) Legs uncrossed, feet flat on floor; 3) Bare arm testing on table; mid-arm at heart level

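### Two LS7 scoring rules for the primary outcome are wrong as written: the whole-grain item appears reversed, and a fasting glucose of 5.6 mmol/L has no score

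*Protocol article*

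**What the plan says.** The LS7 score section of the Protocol article is the only place that sets out the full scoring scheme for the primary outcome. "Each LS7 score metric is evaluated as poor (0 point), intermediate (1 point), or ideal (2 points". "These individual scores are then added together to form a composite score that ranges from 0 to 14". On direction: "A higher LS7 score signifies better cardiovascular health".

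**Diet.** The metric depends on how many of five components are met: "diet (ideal: 4–5 components, intermediate: 2–3 components, poor: 0–1 components". The fifth component is printed as "or less than 3 servings per day of whole grains". Table 2 footnote b lists the same component as "3 servings per day of whole grains (1.1 g of fiber in 10 g of carbohydrate; 1-oz equivalent servings", with no comparison sign. The inclusion criteria use the same rule, by reference to the primary outcome section, for one of the seven risk components: "less than 4 components of healthy diet defined by LS7". Table 2 also uses a diet component count (3 or fewer for low risk, 1 or fewer for high risk) as an input to the NCD risk level.

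**Glucose.** The bands are "FBG (ideal: < 5.6 mmol/L, intermediate: 5.7–6.9 mmol/L, poor: ≥ 7.0 mmol/L". Table 2 gives below 5.6, 5.6–6.9, and 7 or above, and marks fasting glucose as one of the AHA Simple 7 risk factors.

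**The concern.** These rules generate the primary endpoint.

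The whole-grain rule gives a healthy-diet point for eating less whole grain. The sodium and sweets items just before it are genuine upper limits, so a carried-over comparison sign is a plausible cause. If the rule were applied as printed, a participant who rises to three or more servings a day could lose a point where one should be gained.

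The glucose rule leaves one reportable value without a score. Because LS7 is a sum of seven metrics, an unscored metric makes the total undefined or leaves it to an ad hoc decision.

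The diet rule also reaches the diet eligibility criterion and, if the count is made the same way, the NCD risk level in Table 2.

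**Working it through.** **1. The plan's own figure.** Inputs from the sample size section: N = 720, so 720/4 = 180 per arm; difference 0.44; SD 1.57; Bonferroni 0.05/3. The mean of each test statistic is 0.44 / (1.57 × √(2/180)) = 2.66. With three comparisons sharing one control (correlation 0.5), power to reject at least one hypothesis is 0.9005 one-sided, which matches the stated 0.901. Two-sided it is 0.836. The one-sided version is used below.

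**2. Whole grains, per person.** Let k be the number of the other four components met, and w = 1 if whole-grain intake is at least 3 servings a day, otherwise 0. The count is k + (1 − w) as printed and k + w with the sign reversed, so the two always differ by one. Points are 0 for a count of 0–1, 1 for 2–3, and 2 for 4–5.

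| k | ≥3 servings: printed / reversed | <3 servings: printed / reversed |
|---|---|---|
| 0 | 0 / 0 | 0 / 0 |
| 1 | 0 / 1 | 1 / 0 |
| 2 | 1 / 1 | 1 / 1 |
| 3 | 1 / 2 | 2 / 1 |
| 4 | 2 / 2 | 2 / 2 |

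Only k = 1 or k = 3 changes the score, and then by exactly one point. If each other component is met independently with probability p (an assumption; the documents give none), the share affected is 4p(1 − p)[(1 − p)² + p²]:

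- p = 0.05: 0.17
- p = 0.1: 0.30
- p = 0.2: 0.435
- p = 0.3: 0.487
- p = 0.4: 0.499
- p = 0.5: 0.50, the maximum

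**3. Whole grains, arm difference.** Let b be the share of participants at k = 1 or 3, taken as equal in all arms. Let q be the share of them eating at least 3 servings. Printed minus reversed score averages b(1 − 2q) in an arm. If an intervention raises q by d over control, the arm difference falls by 2·d·b. Both d and b are assumed. Power is for 180 per arm, with 0.44 as the true effect under the reversed item and the same loss in all three comparisons.

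| d | b | Loss 2·d·b | Remaining effect | Disjunctive power |
|---|---|---|---|---|
| 0.05 | 0.25 | 0.025 | 0.415 | 0.87 |
| 0.05 | 0.50 | 0.05 | 0.39 | 0.83 |
| 0.10 | 0.50 | 0.10 | 0.34 | 0.72 |
| 0.20 | 0.50 | 0.20 | 0.24 | 0.46 |

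If d = 0 and b is equal across arms, the error cancels.

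**4. Eligibility and risk level.** Whether the count is below 4 changes only at k = 3. Whether it is 1 or fewer changes only at k = 1. Eligibility needs at least two of seven components, so a changed diet criterion matters only where it was decisive.

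**5. Glucose.** Applying the printed bands to a 0.1 mmol/L grid leaves exactly one value unscored, 5.6. On a 0.01 grid, 5.60–5.69 and 6.91–6.99 are unscored. With an assumed normal distribution (mean 4.9–5.3, SD 0.4–0.6), P(5.55 ≤ glucose < 5.65) is 0.022–0.075 per visit. The choice at 5.6 is between 1 and 2 points, so an arm mean moves by at most 0.022–0.075, largely alike in every arm. If an assumed 1–10% of participants lost their LS7 altogether, disjunctive power would be 0.898–0.870.

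**The case against.** The strongest reply is that these are slips in a condensed article. The score is taken from cited definitions, the full version 4 protocol is not shown, and the portal may score correctly. The fish item in the same list also lacks a number of servings, which fits careless transcription. This stands: a reader might infer that trial LS7 values are already misclassified or missing, and the documents do not show that. It does not remove the point, because the printed text is the public definition of the primary outcome. Code that follows it gives wrong or undefined scores; code that does not conflicts with it.

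Second, footnote b carries no sign for any of its five components, so it does not contradict the printed whole-grain rule. That is right. The reversal is an inference, though a strong one: a fibre standard describes what counts towards a target and has little purpose for a food to be limited. The glucose gap needs no inference, since Table 2 contradicts it directly.

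Third, a reader might infer that nearly half of participants are mis-scored and that the trial is therefore biased against the diet-coached arms. Neither follows. The share depends on an assumed p and falls to 17% at p = 0.05. It is also a one-visit, per-person rate, whereas randomisation and adjustment for baseline LS7 leave bias only where the arms diverge. More whole grain costs credit only on reaching 3 servings a day with exactly 1 or 3 other components met. Coached participants are assigned one of three CORE topics, only one of which is diet, and nothing in the article says that whole grain is promoted.

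**Conclusion.** The concern holds as a fault in two stated scoring rules of the primary endpoint.

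The whole-grain item is almost certainly reversed. If applied as printed, it shifts the diet score by one point for roughly 17–50% of participants (assumed p of 0.05–0.5, independent and equal across components). Its effect on an arm difference is about 0.025–0.20 LS7 points against the design effect of 0.44, for assumed d of 5–20% and b of 0.25–0.5. That calculation takes b as equal across arms; if the interventions also change how many other components are met, a further term of either sign is added. The one-point individual error should not be compared directly with 0.44, which is a difference between arm means.

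The glucose gap is certain on the text but small: it concerns classification and completeness and has little effect on power.

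The sample size is unaffected. Actual misclassification depends on the scoring code, which cannot be seen from the article.

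**What to change.** 1. Check the whole-grain item against the LS7 definition the protocol cites and, once confirmed, change it to at least 3 servings per day.
2. Make the glucose bands contiguous and consistent with Table 2: below 5.6, 5.6 to below 7.0, and 7.0 mmol/L or above.
3. Before analysis, verify that the portal's scoring code follows the corrected rules. If it does not, re-derive baseline and 6-month LS7 from the raw items.
4. Reconcile the diet count used for eligibility and for the Table 2 risk level with the corrected rule, and report how many participants' diet risk criterion is affected. Recruitment has ended, so this is a matter of reporting.

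The cost is two wording corrections, a code check and, at most, a re-run of the scoring on raw items. No new data collection and no change to the sample size are needed.

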### Secondary outcomes

#### Biometric data

All biometric data, including SBP, DBP, and biochemical markers (FBG, TC, LDL, high-density lipoprotein (HDL), and TG), were collected at baseline and at the 6-month assessment time point. All parameters will be analyzed and presented as mean ± SD. Analyses will compare the differences between baseline and 6-month values. In addition, all biometric data will be further categorized based on its clinically significant thresholds [47–50].

SBP and DBP are measured by a validated automated office BP (AOBP) device (Microlife WatchBP Office 2G, Microlife Corp., Taiwan). The BP measurement procedures follow the standards of 2021 European Society of Hypertension practice guidelines for office BP measurement [47]. The BP device automatically takes three BP readings within a 1-min interval and provides a mean BP value for analysis, in the absence of healthcare workers to prevent white-coat effects. The device also does not display BP numbers during the 3-min measurement period.

In addition, the 10-year risk of developing CVD of participants at baseline and at the 6-month assessment timepoint will be estimated by QRISK3 score, using participants’ BP, blood cholesterols, BMI, and medical history. QRISK3 estimates an individual’s risk of developing CVD within the next 10 years [51].

#### Lifestyle behavior

Alcohol use will be measured with AUDIT-C at baseline and at the 6-month assessment. AUDIT-C is recommended by the World Health Organization (WHO) to understand the participants’ alcohol consumption risk (e.g., low, hazardous, harmful alcohol use, or alcohol dependence) [52]. Among the shorter versions of the Chinese-translated Alcohol Use Disorders Identification Test (Ch-AUDIT), the AUDIT-C demonstrates the best overall performance, with an area under the curve (AUC) 0.901 compared with 0.898 using Ch-AUDIT [50].

Diet will be assessed by a self-designed questionnaire at baseline and at 6-month assessment. The self-designed questionnaire took references from the Mediterranean diet (MD) and Dietary Approaches to Stop Hypertension (DASH) diet. Dietary frequency and portion intake of grains, fresh fruits, cooked vegetables, raw vegetables, poultry, red meat, processed meat, fish, milk/dairy, beans and nuts, sugar, and wine will be assessed [53]. In addition, a 14-item MD score will be calculated to standardize participant’s dietary habit. A higher score represents better adherence to MD and is associated with lower BMI. 

Physical activity level, including Metabolic Equivalent of Task (MET), total weekly physical activity level, weekly walking duration, and daily sedentary time, will be measured by the Chinese version of International Physical Activity Questionnaire-Short Form (IPAQ-SF) at baseline, at 3-month assessment, and at the 6-month assessment [54]. It contains 7 self-reported items that record how much time during the past 7 days the participant spends on (a) vigorous-intensity activity (e.g, aerobics), (b) moderate-intensity activity (e.g, leisure cycling), (c) walking, and (d) sitting, respectively. A systematic review reported that the IPAQ-SF demonstrated good psychometric properties [55] and has been used among Hong Kong Chinese [54]. All parameters related to physical activity levels will be categorized according to the WHO standards [56].

Sleep quality and disturbances will be measured with the Pittsburgh Sleep Quality Index (PSQI) at baseline and at the 6-month assessment. The PSQI is a 19-item self-rated questionnaire that generates seven components scores, summed to yield a global score ranging from 0 to 21. A higher score indicates higher sleep disturbance [57].

Smoking status of the participants was assessed by categorizing individuals as current smokers (1–10 cigarettes per day, 11–20 cigarettes per day, or more > 20 cigarettes per day), past smokers (having quit smoking within the past 12 months or more than 12 months ago), or non-smokers at baseline, at 3-month, and at the 6-month assessment. The distribution of smoking status at each assessment will be analyzed and compared with that at baseline.

#### Mental health parameters

Perceived stress will be measured with the 10-item Perceived Stress Scale (PSS-10) at baseline and at the 6-month assessment [58, 59]. Participants are asked to rate their feelings and thoughts during the last month on a 5-point Likert scale from 0= never to 4 = very often. It has been used in the Chinese population [60, 61]. The PSS-10 is a validated questionnaire to measure stress in the Chinese community [62, 63].

Anxiety will be assessed by the 7-item Generalized Anxiety Disorder Scale (GAD-7) at baseline and at the 6-month assessment [64]. It is a brief, self-reported scale for identifying probable cases of GAD. The Chinese version has been validated and used in the Chinese population [65, 66]. Participants are asked how often they were bothered by each symptom in the past 2 weeks on a 4-point Likert scale from 0= not at all to 3 = nearly every day. The GAD-7 total score ranges from 0 to 21, with higher scores indicating higher level of anxiety. A score of 0 to 4, 5 to 9, 10 to 14, and 15 to 21 represent minimal, mild, moderate, and severe anxiety, respectively.

Depression will be measured by the 9-item Patient Health Questionnaire-9 (PHQ-9) at baseline and at the 6-month assessment [67]. The Chinese version has been validated and used in the Chinese population [68, 69]. Participants are asked to rate how often they have been bothered by the symptoms in the past 2 weeks on a 4-point Likert scale from 0= not at all to 3 = almost every day. The total score ranges from 0 to 27, with higher score indicating greater level of depression. Scores of 0 to 4, 5 to 9, 10 to 14, 15 to 19, and 20 to 27 represent minimal, mild, moderate, moderately severe, and severe depression, respectively.

Loneliness of participants will be assessed by the validated Chinese version of the 6-item De Jong Gierveld Loneliness Scale. The results will be summed, and a lower total score means more loneliness [70].

Self-efficacy will be measured by the 10-item General Self Efficacy Scale [71]. It assesses self-beliefs to cope with a variety of difficult demands in life. Responses are rated on a 4-point Likert scale from 1= not true at all to 4 = exactly true. It has been used among Chinese [72]. The Chinese version of the 10-item General Self Efficacy Scale has been validated [73].

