**Fig. 1 Fig1:**
[figure not shown]
SPIRIT figure

**Table 1 Tab1:** Baseline risk assessment criteria of seven lifestyle domains

**Domain**	**Reference**	**Domain level**		
		**Poor**	**Intermediate**	**Ideal**
Physical activity	LS7 [91]	None—sedentary	1–149 min/week moderate or intense level of physical activity	≥ 150 min/week moderate or intense level of physical activity
Diet	MD [51]	MD score ≤ 7	8 ≤ MD score ≤ 9	MD score ≥ 10
Sleep	PSQI [53, 92]	14 < Global PSQI score ≤ 21	5 < Global PSQI score ≤ 14	0 ≤ Global PSQI score ≤ 5
Anxiety	GAD-7 [61, 63]	15 ≤ GAD-7 score ≤ 21	10 ≤ GAD-7 score ≤ 14	0 ≤ GAD-7 score ≤ 9
Personal relationship	6-item De Jong Gierveld Loneliness Scale [67]	5 ≤ Loneliness score ≤ 6	2 ≤ Loneliness score ≤ 4	0 ≤ Loneliness score ≤ 1
Alcohol consumption	AUDIT-C [49, 50]	AUDIT-C score ≥ 8	5 ≤ AUDIT-C score < 8	AUDIT-C score < 5
Smoking	LS7 [91]	Current smoker	Former smoker and quit within 12 months	Never smoked, or quit more than 12 months

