The Life's Essential 8 (LE8) composite score at baseline and at 6-month assessment will be calculated using lifestyle and biometric data such as diet, physical activity, sleep duration, smoking status, BMI, BP, FBG, and blood lipid levels. The LE8 score ranges from 0 to 100, with higher scores reflecting a healthier lifestyle and better cardiovascular health [81]. This score is based on the latest guidelines from the AHA for cardiovascular health. Our study was planned before LE8 became available. Therefore, it is included as an exploratory variable.

For continuous secondary outcome measurements—including biometric data (FBG, TC, LDL, HDL, TG, SBP, DBP, and QRISK3 score), lifestyle parameters (AUDIT-C score, physical activity parameters, MD score, PSQI score), mental parameters (PSS-10 score, GAD-7 score, PHQ-9 score, 6-item De Jong Gierveld Loneliness Scale, 10-item General Self Efficacy Scale), quality of life (SF-12, EQ-5D, satisfaction of life scale), and exploratory parameters (BSMAS, 8-item eHealth Literacy score, body composition data, Huawei Watch Fit 2-related parameters, LE8 score), the 6-month and, if available, 3-month assessment data will be compared with baseline values. Data will be presented as mean ± SD. For categorical secondary outcomes, the distribution of each outcome at every assessment time point will be analyzed and compared to baseline. Descriptive statistics (such as counts and percentages) will be presented for each category.

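### The loneliness score runs in opposite directions in the outcome definition and in Table 1, so this secondary outcome could be read the wrong way round

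*Protocol article*

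**What the plan says.** The outcome definition is in the protocol article under Mental health parameters. It names the instrument: "Loneliness of participants will be assessed by the validated Chinese version of the 6-item De Jong Gierveld Loneliness Scale". It then gives the scoring rule: "The results will be summed, and a lower total score means more loneliness". It states no score range and no item coding.

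Table 1, which sets the baseline grading of seven lifestyle domains, uses the same 6-item scale for the personal relationship domain. Its bands are:

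- Poor: "5 ≤ Loneliness score ≤ 6"
- Intermediate: "2 ≤ Loneliness score ≤ 4"
- Ideal: "0 ≤ Loneliness score ≤ 1"

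The score has two uses. At the end of the section Factors for exploratory analysis, the list of continuous secondary outcomes to be compared with baseline includes "6-item De Jong Gierveld Loneliness Scale, 10-item General Self Efficacy Scale". The section Study setting, recruitment, and consent says that problem areas found in the baseline assessment help guide the coaching and the setting of goals.

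**The concern.** A total cannot mean more loneliness at its low end and also be graded Poor at its high end. A participant with a total of 0 or 1 is among the loneliest under the outcome definition and Ideal under Table 1. A participant with 5 or 6 is among the least lonely under the first and Poor under the second.

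What is at stake depends on how the portal actually codes the items. If high means lonelier, the written outcome definition invites a report in which a fall in loneliness appears as a rise. If low means lonelier, the outcome would be read correctly, but the baseline grading of this domain would be upside down for every participant. Under either coding, one of the two uses of the score is wrong as written.

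**Working it through.** The article gives no figure to reproduce here, so the check is a comparison of text plus a short piece of algebra.

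**Step 1. Is it the same score?** Both places name the 6-item De Jong Gierveld scale. They carry different citation numbers (70 in the text, 67 in Table 1). In the text, 67 is attached to the depression questionnaire (PHQ-9), so the difference looks like citation numbering and not a second loneliness instrument.

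**Step 2. Has the table been misread?** The column order of Table 1 can be tested on rows whose direction the text states separately.

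| Scale | Poor band in Table 1 | Direction stated in the text | Agreement |
|---|---|---|---|
| PSQI (sleep) | "14 < Global PSQI score ≤ 21" | higher is worse | yes |
| GAD-7 (anxiety) | 15 to 21 | higher is worse | yes |
| Mediterranean diet score | 7 or less | higher is better | yes |
| Loneliness | 5 to 6 | lower is worse | **no** |

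The first three rows agree with the text, so the Poor-to-Ideal order is sound and the conflict in the loneliness row is not an artefact of the table layout.

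**Step 3. What would a reversal do to the analysis?** The 0 to 6 range comes from the Table 1 bands. Let y be the 6-month score, b the baseline score and T the arm indicator. The planned ANCOVA model is

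y = α + βb + τT + error.

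Put y' = 6 − y and b' = 6 − b. Then

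y' = 6 − α − β(6 − b') − τT − error = (6 − α − 6β) + βb' − τT − error.

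The arm effect becomes −τ. The slope β, the residual variance, the standard error of the arm effect, the absolute test statistic and the two-sided p-value do not change. For illustration only, with a value chosen here and not taken from the article: an adjusted difference of −0.5 points is a benefit if high means lonelier and a harm if low means lonelier. The precision is the same in both cases, so nothing in the model output would show which reading is right.

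**Step 4. The two possible cases.**

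| True coding of the portal | Outcome read by the written definition | Baseline grade by Table 1 |
|---|---|---|
| High = lonelier | reversed: benefit described as harm | correct |
| Low = lonelier | correct | inverted: loneliest graded Ideal, least lonely graded Poor |

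**Step 5. Which is likelier?** Grading 0 to 1 as Ideal for personal relationships makes sense only if a low total means less loneliness. Table 1 also gives three bands that are consistent with each other, whereas the outcome definition rests on a single clause. That favours Table 1 but does not prove it, because neither place shows the item coding.

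**The case against.** The strongest case on the other side is that nothing in the planned calculation uses the disputed sentence. The comparison with baseline, the mean ± SD and the ANCOVA all run on the stored scores. If those are coded as Table 1 implies, the estimate is correct whatever the prose says, and the sentence may be no more than a slip. This is right, and it limits the point to interpretation.

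Some stronger readings are tempting, but the documents do not support them:

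- **That the result will be published with the wrong sign.** This needs two things together: scores coded with high as lonelier, and authors who interpret them by the written definition. Nothing in the article shows that both will happen.
- **That the error has a size in points.** A move from 5 to 1 could be misread as a 4-point deterioration, but that describes one hypothetical participant. It is neither an expected effect nor a bias in a planned contrast.
- **That Table 1 decides what is coached.** The article says that problem areas guide the sessions. Priorities are agreed jointly by coach and participant, and the CORE topic also depends on preference. Coaching intensity follows Table 2, which has no loneliness item.
- **That the outcome definition is proven wrong.** It cites a source for the scale that is not at hand, and the bands are indirect evidence.

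The reach is also small. The loneliness scale is one of 20 entries in the secondary list (8 biometric, 4 lifestyle, 5 mental and 3 quality of life, as grouped there), and the Statistical analysis section places the secondary outcomes under exploratory analyses.

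The contradiction itself survives. It is not a detail left to an analysis plan or a fuller protocol: the article states two incompatible directions for a named outcome.

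**Conclusion.** The contradiction is certain; its consequence is conditional. As written, the loneliness outcome could be interpreted in the wrong direction, with benefit read as harm or the reverse. If the outcome definition describes the true coding, the baseline personal relationship grade is inverted instead. Where a reversal occurs it is complete in direction and nil in magnitude: the absolute estimate, standard error and two-sided p-value stay the same.

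This rests on two assumptions: that both places refer to one summed score with the 0 to 6 range implied by Table 1, and that no reverse coding reconciles them outside the article. The impact is limited to one secondary outcome and one baseline domain level. The LS7 score, the sample size and the power are unaffected. It should be corrected before analysis, but it does not threaten the trial's main conclusion.

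**What to change.** Take the steps in this order, because the first settles the rest.

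1. Check how the portal codes and sums the six items, including any reverse-scored items, at baseline and at 6 months, and confirm that both visits use the same coding. If only one visit were reversed, a change from baseline would become 6 − x₁ − x₀ in place of x₁ − x₀ (x₀ baseline, x₁ 6 months), which has no meaning as a change.
2. State one direction and the score range in the outcome definition.
3. Correct whichever place disagrees with the verified coding. Most likely this is the sentence under Mental health parameters, which would then say that a higher total means more loneliness. If the check shows the opposite, the Table 1 bands need to be reconciled instead, and the baseline grades already issued for this domain should be reviewed.

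The cost is one sentence (or one table row) and a check of the scoring code. No new data are needed, and no primary analysis changes. The article reports that recruitment had ended by 30 September 2024 and that two participants had completed final assessments by 29 October 2024, so baseline scores exist against which the coding can be verified.
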